## Abstract

**Background:**

Low transsphincteric fistulas less than 1/3 of the sphincter complex are easy to treat by fistulotomy with a high success rate. High transsphincteric fistulas remain a surgical challenge. Various surgical procedures are available, but recurrence rates of these techniques are disappointingly high. The mucosal flap advancement is considered the gold standard for the treatment of high perianal fistula of cryptoglandular origin by most colorectal surgeons. In the literature a recurrence rate between 0 and 63% is reported for the mucosal flap advancement. Recently Armstrong and colleagues reported on a new biologic anal fistula plug, a bioabsorbable xenograft made of lyophilized porcine intestinal submucosa. Their prospective series of 15 patients with high perianal fistula treated with the anal fistula plug showed promising results.

The anal fistula plug trial is designed to compare the anal fistula plug with the mucosal flap advancement in the treatment of high perianal fistula in terms of success rate, continence, postoperative pain, and quality of life.

**Methods/design:**

The PLUG trial is a randomized controlled multicenter trial. Sixty patients with high perianal fistulas of cryptoglandular origin will be randomized to either the fistula plug or the mucosal advancement flap. Study parameters will be anorectal fistula closure-rate, continence, post-operative pain, and quality of life. Patients will be followed-up at two weeks, four weeks, and 16 weeks. At the final follow-up closure rate is determined by clinical examination by a surgeon blinded for the intervention.

**Discussion:**

Before broadly implementing the anal fistula plug results of randomized trials using the plug should be awaited. This randomized controlled trial comparing the anal fistula plug and the mucosal advancement flap should provide evidence regarding the effectiveness of the anal fistula plug in the treatment of high perianal fistulas.

**Trial registration:**

**ISRCTN: **97376902

## Background

A perianal fistula is a common condition. It has an incidence of 5.6 per 100.000 in women and 12.3 per 100.000 in men [1]. The disease occurs predominantly in the third and fourth decade of life [2]. It is believed that infection of the intersphincteric glands is the initiating event in fistula in ano, in a process known as the 'cryptoglandular hypothesis' [3].

Parks *et al. *[4] developed a classification system in which fistula are divided into intersphincteric fistula, transsphincteric fistula, suprasphincteric fistula and extrasphincteric fistula. However the type of treatment depends not on the location of the fistula tract but of the level of the internal opening in the anal canal.

Low transsphincteric fistulas comprising less than 1/3 of the external sphincter complex are easy to treat by fistulotomy with a high success rate. High transsphincteric fistulas remain a surgical challenge. Surgical procedures include advancement flaps, loose-seton placement, and the installation of fibrin glue. All of these techniques have disappointing success rates. In the literature a recurrence rate between 0 and 63% is reported for the mucosal flap advancement [5-7]. Recently, Van der Hagen *et al. *[6] published the result of 41 patients with high transsphincteric, suprasphincteric and extrasphincteric fistula treated with a mucosal flap advancement. The success rate was a mere 37% (with a median follow-up of 72 months).

The fibrin glue is an alternative to the mucosal advancement flap, however long-term closure rates are low [8-14]. The percentages being as low as 16 percent. The liquid consistency of fibrin glue is possibly not ideal for the purpose of closing anorectal fistulas, because the glue is easily extruded from the fistula tract by increased pressure [15].

Armstrong and colleagues reported a new biologic anal fistula plug [16]. The plug is a FDA and CE approved bioabsorbable xenograft, made of lyophilized porcine intestinal submucosa by Cook Surgical, Inc., Bloomington, IN. The material has inherent resistance to infection, produces no foreign body or giant cell reaction, and becomes repopulated with host cell tissue during a period of three months. The material was fashioned into a conical plug and secured into the primary opening of the fistula tract. Armstrong achieved promising results in a prospective series of 15 patients treated with the anal fistula plug. They compared the results with ten patients using fibrin glue. Patients with high anorectal fistulas (high transsphincteric or deeper) were included. Excluded were patients with Crohn's disease or superficial fistulas (low transsphincteric or more superficial). At a median follow-up of 13.8 ± 3.1 weeks they achieved a significant better fistula closure rate of 87% compared to the fibrin glue group (P < 0.05).

These results call for a prospective randomised controlled trial. Since mucosal flap advancement is the preferred treatment for high cryptoglandular perianal fistula, the anal fistula plug will be compared with mucosal flap advancement in a randomised setting.

## Methods/design

### Study objectives

The objective of this study is to compare, in a prospective randomized way, the anal fistula plug with the mucosal advancement flap in the treatment of high transphincteric perianal fistula in terms of fistula closure rate, continence, morbidity, postoperative pain, and quality of life.

### Study design

The PLUG trial is a prospective double blinded randomized multicenter trial. Patients with high perianal fistulas of cryptoglandular origin will be randomized to either the fistula plug or the mucosal advancement flap. Randomization will be performed during surgery after finding the internal opening. The computer randomization will be done centrally in the Academic Medical Centre in Amsterdam, the Netherlands. Stratification is performed for the randomizing centers.

Patients will be blinded for the type of intervention i.e. anal fistula plug or mucosal advancement flap. Patients are followed-up at two weeks, four weeks, and 16 weeks. At the final follow-up closure rate is determined by clinical examination. Follow-up is done by a colorectal surgeon, who is blinded for the type of intervention. The fistula will be rated closed if the external and the internal opening are closed and no discharge is experienced. Otherwise it is considered as a persistent fistula.

### Study population

The study population consists of patients with high perianal fistulas.

Inclusion criteria are; age above 18 years, high anorectal fistula of cryptoglandular origin (transsphincteric, upper 2/3 of the sphinctercomplex which is confined by the puborectal sling and the end of the anal canal), and informed consent.

Exclusion criteria are; no internal opening found during surgery, HIV-positive patients, Crohn's disease, malignant cause, tuberculosis, hydradenitis suppurativa, and pilonidal sinus disease.

### Primary and secondary endpoints

The primary endpoints of the PLUG trial are fistula closure rate and continence. Continence will be evaluated pre- and postoperatively using the COREFO, the Wexner and the Vaizey score. The COREFO questionnaire has 27 questions to asses colorectal functional outcome [17]. The Vaizey scale consists of three items about the type (gas, fluid, solid) and frequency of incontinence (all scored from zero to four) and four additional items that address alteration in lifestyle (zero to four), the need to wear a pad or plug (zero or two), the use of constipating medication (zero or two), and the lack of ability to defer defecation for 15 minutes (zero or four). The total score on the Vaizey scale ranges from 0 (complete continence) to 24 (complete incontinence) [18].

Secondary endpoints are morbidity, postoperative pain, and quality of life. Postoperatively patients will be asked to grade their pain on a visual analogue scale (VAS: 0, no pain; 10, worst imaginable pain) on different moments during the follow-up. Quality of life will be evaluated using the SF-36 questionnaire. The SF-36 measures eight health attributes: physical functioning, social functioning, role limitations due to physical problems, role limitations due to emotional problems, mental health, pain, vitality and general health perception. The higher the score, the better the health rating with 100 points as the maximum for each concept. In addition the EQ-5D questionnaire is used.

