#### Sample size calculation

A success percentage of 87% was reported by Armstrong and colleagues for the anal fistula plug [16]. For the mucosal advancement flap a success percentage of 37% was reported recently by Hagen and colleagues in a series of 41 patients with a follow-up of 72 months [6].

To detect an increase in success percentage from 40% to 80%, using a significance level of 0.05, at least 46 patients have to be randomized to achieve a power of 80%. In total, 60 patients will be randomized.

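### Closure and continence are both primary, but the 0.05 level and the sample size are worked out for closure only, so they do not cover the declared primary question

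*Protocol article*

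**What the plan says.** Under Primary and secondary endpoints, the protocol article gives two outcomes primary rank without ordering them: "The primary endpoints of the PLUG trial are fistula closure rate and continence". Morbidity, pain and quality of life are placed below them as secondary. The same section adds: "Continence will be evaluated pre- and postoperatively using the COREFO, the Wexner and the Vaizey score". None of the three scores is marked as the leading one.

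Under Sample size calculation there is one calculation: "To detect an increase in success percentage from 40% to 80" per cent, "using a significance level of 0.05", for which "at least 46 patients have to be randomized to achieve a power of 80" per cent. The section ends: "In total, 60 patients will be randomized". The success percentages are closure rates taken from earlier series. No difference, standard deviation or margin for continence appears anywhere in the article.

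Under Statistical analysis, apart from the sample size, only the intention-to-treat principle is stated.

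**The concern.** A significance level and a power figure describe a decision. Here the decision involves two primary endpoints, while the 0.05 and the 80% belong to one of them. The article does not say whether the trial succeeds on either endpoint or only on both, and the two rules have different consequences. An either-endpoint rule with each test at 0.05 raises the chance of a false primary claim. A both-required rule keeps that chance in check, but the trial's power is then no longer the power for closure.

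Continence is the weaker half under both rules. It has primary rank but no sizing basis, and three scores could each be presented as the primary result. The Discussion gives preserved continence as part of the treatment aim and sphincter safety as an advantage of the plug. A non-significant continence comparison might therefore be reported as a primary finding of preserved continence, although the trial was never sized to support one.

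**Working it through.** **Inputs.** From Sample size calculation: closure 40% (flap) and 80% (plug), alpha 0.05, power 80%, minimum 46, planned 60. Assumed, because the article does not state them: two-sided tests, 1:1 allocation (23 or 30 per arm), uncorrected chi-square.

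**1. The plan's own figure.** Per arm, n = [z(1−α/2)·√(2·p̄(1−p̄)) + z(power)·√(p1(1−p1)+p2(1−p2))]² / (p2−p1)², with p̄ = 0.6.

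- First term: 1.960 × √0.48 = 1.358.
- Second term: 0.842 × √(0.24 + 0.16) = 0.532.
- n = (1.358 + 0.532)² / 0.16 = 22.3, so 23 per arm and 46 in total. The stated 46 is reproduced.

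**2. Closure power.** Power = Φ{[(p2−p1)·√n − z(1−α/2)·√(2·p̄(1−p̄))] / √(p1(1−p1)+p2(1−p2))}. For example, with n = 30 at 0.05: Φ[(0.4 × 5.477 − 1.358) / 0.632] = Φ(1.317) = 90.6%.

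| Level for closure | Total needed for 80% | Power, 46 evaluable | Power, 60 evaluable |
|---|---|---|---|
| 0.05 | 46 | 81.2% | 90.6% |
| 0.025 (two-way split) | 56 | 71.8% | 84.3% |
| 0.0125 (four-way split) | 66 | 61.7% | 76.7% |

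With Fisher's exact test, power at 60 is 85.1% at 0.05 and 77.2% at 0.025.

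**3. If a win on either endpoint counts, each test at 0.05.**

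- Closure plus one continence scale, independent: 1 − 0.95² = 9.75%.
- Closure plus three separately tested scales, all independent: 1 − 0.95⁴ = 18.5%.
- Closure independent of the scales, and the three scales correlated with each other (simulation, one million replicates; correlations assumed): 17.0% at 0.5, 15.4% at 0.7, 14.3% at 0.8, 13.1% at 0.9.

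Under this rule, power to win on at least one endpoint is no lower than closure power, 90.6% at 60.

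**4. If both must be won.** Familywise error is at most 5%. Joint power cannot exceed the power for continence, which the article gives no means of computing. For illustration, take one scale, 30 per arm, independence, the normal approximation, and assumed standardised differences:

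- 0.3 SD: 0.906 × 0.212 = 19%
- 0.5 SD: 0.906 × 0.491 = 44%
- 0.8 SD: 0.906 × 0.873 = 79%

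**5. What 30 per arm can detect on continence.** The normal approximation with 80% power is (z(1−α/2) + z(0.80)) × √(2/30). This gives (1.960 + 0.842) × 0.258 = 0.72 SD at 0.05, and (2.241 + 0.842) × 0.258 = 0.80 SD at 0.025. A two-sample t-test gives slightly more: 0.74 SD and 0.81 SD. For a 0.5 SD difference at 0.05, 80% power would need 126 patients in total.

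**The case against.** The best defence is that the sample size section claims nothing about a joint question. Its 0.05 and 80% are attached to closure, and 46 reproduces exactly for that. The trial also randomises 60. If all are evaluable, closure keeps 84.3% power after a two-way split of alpha. A decision rule, an alpha split and the choice of a lead scale may stand in an analysis plan that is not shown, and a condensed article need not repeat them. All of this stands, and it rules out several stronger readings that a reader might infer:

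- **Both the error rate and the power fail.** No single decision rule does this. The either rule raises error without reducing the power to win on at least one endpoint. The both rule lowers joint power without raising error.
- **The false-positive risk is 18.5%.** This needs four separate, independent confirmatory tests. The article says that continence is evaluated on three instruments, not that each is tested as a primary endpoint. Scores of the same function are also unlikely to be independent.
- **Closure is underpowered.** Under the uncorrected chi-square, power falls below 80% only with a four-way split, or if losses bring the evaluable number close to 46 after a two-way split. The article does not say that the extra 14 are an allowance for losses. Fisher's exact test at 0.025 would also fall short, but the article names no test.
- **The lack of a multiplicity rule is itself an error.** It may be in the analysis plan.
- **The three scales duplicate each other.** Only the Vaizey items are listed, so overlap is an inference.

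What the defence does not remove is the mismatch in the text itself. Endpoint rank and sample size are both fixed here. An analysis plan could add an alpha rule, but it could not change the fact that the trial was sized without any continence input.

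**Conclusion.** The concern holds in this limited form: two endpoints are declared primary, and the level and sample size are worked out for one. The closure figures are correct, but they do not extend to the primary question as declared. The consequence depends on a rule that the article does not fix:

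- **Either suffices:** familywise error up to 9.75% with one continence scale, and about 13% to 17% in the worst case of three separately tested scales.
- **Both required:** error at or below 5%, but joint power unknown and not described by the 80%.
- **Under either rule:** continence has 80% power only for a difference of about 0.74 SD at 0.05 or 0.81 SD at 0.025.

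These figures assume 1:1 allocation, two-sided tests, 60 evaluable patients and, for the worst case, scale correlations of 0.5 to 0.9. The mismatch itself needs none of these assumptions.

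**What to change.** **Preferred.** Name fistula closure at 16 weeks as the single primary endpoint, because the trial is sized on it. Make continence on one scale, named in advance, the key secondary endpoint. Vaizey is one candidate, being the scale that the article itemises, but the choice should rest on clinical relevance. Report the continence difference with a confidence interval whatever the closure result, so that it remains informative if closure does not differ. Treat the other two scales as supportive.

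**Alternative.** Keep both as primary on one named continence scale and:

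- state whether either endpoint suffices or both are required;
- apply Holm or Bonferroni if either suffices;
- restate closure power as about 84% at 0.025 with 60 evaluable patients (uncorrected chi-square);
- state the continence difference that 60 patients can detect: about 0.74 SD at 0.05, or 0.81 SD at 0.025.

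**Cost.** Both routes change wording in Primary and secondary endpoints and in Sample size calculation, and neither adds patients. Under the first, continence loses its nominal primary status. Under the second, if alpha is split, closure power falls from about 91% to 84%. If both are required, the alternative does not make the trial adequately powered for a smaller continence difference; it only makes that limit visible.

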### Data collection and monitoring

Data are collected via datasheets on paper, which are sent to the Academic Medical Centre by mail. Postoperatively questionnaires on pain are filled in by patients. Sixteen weeks after surgery questionnaires are sent to the patients to assess continence and quality of life.

There will be regular contact between the study coordinators and the participating centers. One research fellow will monitor the included data of every patient.

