## Discussion

The main objective in the treatment of perianal fistula is the healing of the fistula by closing the internal opening while preserving the anal continence. Submucosal, intersphincteric, and low transsphincteric fistulas, in the lower one-third of the external sphincter complex are easy to treat by simple fistulotomy, with a favourable success rate and relatively little impact on faecal continence [19,20]. The surgical treatment of high perianal fistulas of cryptoglandular origin in relation to morbidity remains a difficult problem. The anal fistula plug appears to be a promising alternative to the current treatment options for high perianal fistulas [20-24]. The anal fistula plug is fabricated from porcine collagen which stimulates tissue remodelling leading to full closure the fistulous tract. Furthermore, the advantage of the plug is that it can be used repeatedly, without risk of damaging the anal sphincter. In a recent study describing the results of the surgical treatment of perianal fistulas of cryptoglandular origin soiling was reported following surgery in 40% of the patients [25]. In these series 109 patients were treated by fistulotomy for low perianal fistulas. A rectal advancement flap was performed in 70 patients for high transsphincteric fistulas. Another advantage is that installing the plug is minimally invasive with possibly less postoperative pain. During mucosal flap advancement, the fistula tract is excised externally to the anal sphincter in order to ensure an optimal drainage.

Before broadly implementing the anal fistula plug results of randomized trials using the plug should be awaited. This randomized controlled trial comparing the anal fistula plug and the mucosal advancement flap should provide evidence regarding the effectiveness of the anal fistula plug in the treatment of high perianal fistulas.

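### Pain is scored only after surgery, so the arm comparison forgoes a modest gain in precision that one preoperative VAS item would give

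*Protocol article*

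**What the plan says.** Pain is a secondary endpoint of the protocol article: "Secondary endpoints are morbidity, postoperative pain, and quality of life" (Primary and secondary endpoints). The measure is a 0–10 visual analogue scale, and its timing is given twice. The endpoints section says "Postoperatively patients will be asked to grade their pain on a visual analogue scale", with scores taken "on different moments during the follow-up". Data collection and monitoring says "Postoperatively questionnaires on pain are filled in by patients". Neither place mentions a score before surgery.

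For continence the endpoints section is explicit about both times: "Continence will be evaluated pre- and postoperatively using the COREFO, the Wexner and the Vaizey score".

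The SF-36 also touches on pain, since its attributes include "role limitations due to emotional problems, mental health, pain, vitality and general health perception". The only stated time for quality-of-life forms is late: "Sixteen weeks after surgery questionnaires are sent to the patients to assess continence and quality of life".

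Randomisation takes place centrally during the operation, and patients are blinded (Study design). Sixty patients are planned (Sample size calculation).

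**The concern.** Postoperative pain is among the study objectives, and the Discussion offers it as a possible advantage of the plug: "installing the plug is minimally invasive with possibly less postoperative pain". A trial of 60 patients estimates a pain difference with limited precision, so an inexpensive gain is worth having.

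If patients differ in pain before surgery, and those differences carry over in part to later scores, a preoperative score explains some of the spread in the postoperative VAS. Without it that spread remains in the residual variance, and a chance imbalance in preoperative pain cannot be adjusted for. A preoperative score cannot be obtained once the patient has been operated on, so the choice has to be made before enrolment.

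**Working it through.** **The plan's own figure.** The article gives no figure for pain. Its one sample-size figure concerns closure (40% v 80%, significance level 0.05, power 80%, 46 patients). With a two-sided test, pooled variance and no continuity correction:

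n per arm = [1.960·√(2·0.6·0.4) + 0.842·√(0.4·0.6 + 0.8·0.2)]² / 0.4² = (1.358 + 0.532)² / 0.16 = 22.3, rounded up to 23, so 46 in total.

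The figure reproduces, but it has no bearing on the precision of the pain comparison.

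**Inputs for pain.**
- From the article: 60 patients; VAS from 0 to 10.
- Assumed: equal allocation (30 per arm); SD of the postoperative VAS 2.5 points, with a range of 1.5 to 3.0; correlation ρ between preoperative and postoperative VAS from 0 to 0.7; for the power figures only, a true difference of 1.5 points and a two-sided 5% test. The article gives none of these.

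**Step 1: unadjusted comparison.** SE = SD·√(2/30) = 0.258·SD. At SD 2.5 this is 0.645 points. The 95% confidence interval half-width is 1.96 × 0.645 = 1.27, and the difference detectable with 80% power is (1.960 + 0.842) × 0.645 = 1.81.

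**Step 2: adjusted for a preoperative VAS.** The SE is multiplied by √(1 − ρ²), and the equivalent unadjusted sample size is 60/(1 − ρ²). The approximate cost of estimating one more coefficient is a further factor √(1 + 1/56) = 1.009. The half-width and power columns leave this small factor out.

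| ρ | SE multiplier | with cost of covariate | equivalent N | half-width (SD 2.5) | power for 1.5 points (SD 2.5) |
|---|---|---|---|---|---|
| 0 | 1.000 | 1.009 | 60 | 1.27 | 64% |
| 0.2 | 0.980 | 0.989 | 62.5 | 1.24 | 66% |
| 0.3 | 0.954 | 0.962 | 65.9 | 1.21 | 68% |
| 0.5 | 0.866 | 0.874 | 80.0 | 1.10 | 77% |
| 0.7 | 0.714 | 0.720 | 117.6 | 0.90 | 90% |

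The SE multiplier does not depend on the SD. The power does. For the same 1.5 points, going from no adjustment to ρ = 0.3 and then ρ = 0.5, power is 97%, 98% and 99% at SD 1.5; 83%, 86% and 92% at SD 2.0; and 49%, 53% and 61% at SD 3.0.

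**Step 3: chance imbalance.** The difference between arms in mean preoperative pain has expectation zero and SE 0.258 SD. An imbalance of that size shifts the unadjusted postoperative difference by ρ × 0.258 SD. Taking the same SD of 2.5 before surgery, that is 0.3 × 0.645 = 0.19 points at ρ = 0.3 and 0.5 × 0.645 = 0.32 points at ρ = 0.5. This is not additional to Step 1, because the unadjusted SE already contains it. Adjustment removes it.

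**The case against.** The strongest case against is that nothing here is wrong. The endpoint is named postoperative pain and is measured postoperatively, and the two sections agree. Randomisation balances preoperative pain in expectation, and chance imbalance is already in the standard error. Continence is a primary endpoint concerned with preserving function, so a before-and-after score there does not oblige the plan to do the same for pain. The entry criteria set no pain threshold, and nothing in the article says how well fistula pain predicts pain after the operation. All of this stands, and it limits the point to an optional gain in precision. It does not remove the gain if ρ is moderate. The timing is also something the article states, in contrast with continence, and not merely a silence.

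A reader might infer four stronger things, which the document does not support.

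- *That analgesic use goes unrecorded.* The article does not mention analgesics, but it is condensed and shows neither the pain questionnaire nor the datasheets. Their content is unknown.
- *That the pain difference is pulled toward zero.* This would need greater analgesic use, or greater relief, in the more painful arm. The article establishes neither. With equal use and equal relief there need be no distortion, and pain felt under usual pain relief is a legitimate quantity to compare. Recording analgesics would give context, but it would change neither the VAS difference nor its standard error.
- *That the missing preoperative score biases the comparison.* It does not, because allocation is random.
- *That the VAS is the only pain measure.* The SF-36 has a pain attribute. With its stated timing at 16 weeks, though, it covers no early postoperative pain and supplies no stated preoperative value.

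**Conclusion.** The point holds as a cheap improvement to a secondary endpoint. As described, the pain comparison cannot use preoperative pain to reduce residual variance. For an assumed correlation of 0.3 to 0.5, adjustment would lower the standard error by about 5% to 13%. At SD 2.5 the confidence interval half-width would go from 1.27 to between 1.21 and 1.10 points. At a correlation of 0.2 the reduction is about 2%. At zero there is no gain, and the standard error rises by about 1%.

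The size rests on a correlation that the article does not give, and the figures in VAS points and power rest also on an assumed SD and true difference. There is no bias and no contradiction. If the full protocol, which is not shown, already includes a preoperative VAS, only the article's wording needs to change.

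**What to change.** - Add one 0–10 VAS item to the preoperative assessment that Primary and secondary endpoints already states for continence. Because randomisation takes place during surgery, a score taken beforehand cannot be influenced by allocation and is a valid covariate.
- In Primary and secondary endpoints and in Data collection and monitoring, state that pain is measured both before and after surgery.
- Compare postoperative VAS between arms adjusted for the preoperative score, for example by analysis of covariance, and name that covariate in advance.

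The cost is one extra item per patient and one covariate in the model. It needs no extra visits or patients.
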